#### Study participants

Study participants

The study will invite nursing students who have opted for the elective course "Cultural Perspectives on Death and End-of-Life Education" at a medical university in Southwest China between 1 March 2026 to 30 April 2026 to participate in this study. Written informed consent will be obtained from all participants. Students will be invited if they:(1)have not previously enrolled in the "Cultural Perspectives on Death and End-of-Life Education" course;(2)are free from severe psychological or physical conditions;and (3)have granted informed consent.Students will be excluded if they:(1)have previously received education or training in palliative care;and (2)have been diagnosed with significant learning impairments.

#### Control Group

The control group will engage in conventional classroom teaching, which will last for 90 minutes and will be conducted by a seasoned lecturer with expertise in nursing. This teaching session will mirror the key points and utilize the same case themes as those found in the VCS system.

#### Intervention Group

Participants in the intervention group will receive the same 90 minutes of classroom teaching as the control group, but they will additionally interact with a VCS system specifically developed for palliative care education by the research team.

**Intervention content**

The VCS system leverages 3D modeling technologies via Java and VRML to craft immersive environments that mimic actual hospice settings, encompassing hospital wards, medical equipment, and representations of patients, their families, and healthcare workers. Participants will assume the role of virtual nurses, engaging with non-player characters (NPCs) to adeptly navigate patient care, thereby addressing both patient and family needs.After the 90-minute conventional classroom teaching, each participant will be assigned a unique code for accessing the VCS system, which will enable research assistants to effectively track participant engagement by monitoring their login activity on the system's backend.The VCS system is meticulously organized into three comprehensive modules: the Basic Knowledge Module, the Practice Theatre Module, and the Knowledge Testing Module.In the Basic Knowledge Module(Fig.2), participants will be introduced to basic knowledge about major concepts in palliative care. Learners will acquire a solid understanding of palliative care, its core principles, essential knowledge, psychological support for the terminally ill patient, guidelines for counselling the grieving, recognition of common clinical presentation at the end of life, and updates on EOLC practices.The Practice Theatre Module focuses on the case of an 89-year-old elderly male patient with advanced lung cancer who is admitted to a palliative care ward for hospice care(Fig. 3).This module features six detailed learning scenarios: Case Introduction, Admission Care, Specialized Nursing, Spiritual Care, Social Support, and EOLC.Each scenario includes a variety of contextual educational tasks such as choices, dialogues, and reading assignments, engaging learners in decision-making processes. Learners will interact with the VCS environment by clicking on navigation icons and using menu controls on the screen, guided by an automated assistant. Additionally, the system will evaluate the "correctness" of each task choice, assign scores, and automatically log these data in the backend.Such interactions will empower virtual nurses to perform assessments, physical exams, select medical tools, execute appropriate interventions, and maintain effective communication. The overarching aim is to enhance terminally ill patients' quality of life. Furthermore, this module will seek to cultivate a compassionate attitude and holistic palliative care ability among students, thus enabling them to promptly and accurately identify and address the physiological, psychological, and emotional issues of terminally ill patients when faced with end-of-life situations. It will also promote the development of critical clinical thinking and ethical decision-making abilities. The Knowledge Testing Module will present 10 randomized questions, awarding 1 point for each correct response(Fig. 4).The system will generate experimental reports based on different scenarios, which encompass the correct task answers, the options selected by users, and their final scores.These reports will specify the steps or knowledge points that remain incomplete, and can be readily archived by users for future reference when conducting additional experiments. Furthermore, these reports will offer invaluable insights to facilitate students' reflective learning processes.

[figure not shown]

Fig. 2: The Basic Knowledge Module

[figure not shown]

Fig. 3: The Practice Theatre Module

[figure not shown]

Fig. 4: The Knowledge Testing Module

**Primary Outcomes**

1.**Nurses' Palliative Care Knowledge Scale**

2.**The Undergraduate Nursing Students' Palliative Care Ability Assessment Questionnaire**

3.**The Chinese Version of the Frommelt Attitudes Toward Care of the Dying Scale Form B (FATCOD-B)**

**Secondary Outcomes**

1.Student Satisfaction and Self-confidence in Learning Scale

**Sample Size**
The determination of the necessary sample size for this investigation was conducted conducted using G*Power 3.1.9 software[15],employing a two-tailed independent t-test with an alpha level of 0.05, a power of 0.90, and an effect size of 0.71[16]. Taking into account a 10% attrition rate，at least 48 students per group were needed to achieve this statistical power for the study.

**Data Collection**
Data Collection

Seven days after their initial meeting, both groups will undergo baseline assessments of their palliative care knowledge, ability, and attitudes (pre-intervention, T0). After the intervention, post-intervention assessments (T1) will be conducted to evaluate the participants' palliative care knowledge, ability and attitudes. In addition, students in the intervention group will be invited to complete the Student Satisfaction and Self-confidence in Learning Scale at the end of the intervention.Following the T1 assessment, the control group will receive the same VCS intervention as the intervention group.

**Data Analysis**
We will use SPSS 26.0 statistical software to analyze the data. When the data follow a normal distribution, descriptive statistics (mean and standard deviation) will be used to represent the central tendency and dispersion for continuous demographic data (e.g., age), as well as for ratings of palliative care knowledge, ability, and attitudes. For data that do not follow a normal distribution, the median and interquartile range will be utilized to depict central tendency and variability.We will use frequencies and percentages to represent categorical data, such as gender. Independent t-tests will be used to examine whether there are significant differences in the mean demographic data between the intervention and control groups. Chi-square tests will be employed to compare the distribution of sample characteristics between the two groups for homogeneity. Independent t-tests will also be used to compare the levels of palliative care knowledge, ability, and attitudes between the intervention and control groups. To compare the overall scores and scores across different dimensions of palliative care knowledge, ability, and attitudes before and after the VCS education system intervention, researchers will use paired t-tests to assess the changes in these levels in the students. A two-tailed p<0.05 is considered statistically significant.

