#### Fig. 1 Flowchart of the study design

#### Randomization and blinding

Every student enrolled in the course will receive an invitation via email to join as research volunteers. Those who consent will participate in an initial meeting where they will sign informed consent forms. Subsequently, these volunteers will be asked to complete a detailed questionnaire that collects their sociodemographic data and academic performance, including their average course grades.This information will then be utilized to facilitate the randomization process. To preserve confidentiality, each student will choose a unique six-digit identifier. An impartial research assistant, who will not participate in the educational activities, will utilize SPSS 26.0 statistical software to allocate students evenly into either the control or intervention group with a 1:1 ratio.Seven days after their initial meeting，and following the completion of the randomization procedure, all students who will have volunteered for the study will be invited to meeting again. This subsequent meeting will be organized to conduct a comprehensive baseline evaluation of their knowledge, ability, and attitudes concerning palliative care.This initial assessment, referred to as the pre-intervention assessment, serves to establish a benchmark against which future improvements can be measured.During this meeting, participants will be informed of their group placement through their unique identifiers and will then be directed to the appropriate classrooms for a briefing on their respective group assignments.

Due to the specific nature of the intervention, conducting a double-blind trial will be deemed unfeasible. Nonetheless, a single-blind design will be implemented by keeping the group assignments hidden from both the research assistants and the instructors.

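### The between-group t-tests on the three primary outcomes make no use of the baseline scores; ANCOVA on T0 would gain precision with no extra students or measurements

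*Protocol*

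**What the plan says.** The Data Analysis section names the between-group test for the primary outcomes: "Independent t-tests will also be used to compare the levels of palliative care knowledge, ability, and attitudes between the intervention and control groups". It mentions no covariate and no time point. Change from before to after is handled separately: "researchers will use paired t-tests to assess the changes in these levels in the students". The Sample Size section plans on the same unadjusted two-sample t-test.

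Under Data Collection, both groups are assessed on the three constructs at T0, and afterwards "post-intervention assessments (T1) will be conducted to evaluate the participants' palliative care knowledge, ability and attitudes". Randomization and blinding says that the T0 assessment "serves to establish a benchmark against which future improvements can be measured".

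The same section describes a questionnaire, given before randomisation, that "collects their sociodemographic data and academic performance, including their average course grades". It then says: "This information will then be utilized to facilitate the randomization process". The mechanism is not described beyond software that will "allocate students evenly into either the control or intervention group with a 1:1 ratio". No analysis step uses these variables as covariates. Demographics and sample characteristics are tested between groups at baseline, but nothing is said to follow from the result.

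**The concern.** The protocol collects, for every student, a baseline value of each primary outcome, and gives that baseline the role of reference for improvement. The randomised comparison then sets it aside. The analysis that does use T0 for change looks at students before and after, so it cannot separate the effect of the simulation from the effect of the classroom teaching that both groups receive.

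Two things are at stake. The first is precision: part of the spread in T1 scores is spread that was already there at T0, and removing it would narrow the interval for all three primary outcomes. The second is interpretation of the single trial that will be run: if the groups differ by chance at T0, the unadjusted T1 difference carries part of that gap, and the plan has no step that corrects for it. Because the protocol itself names the test, this is a choice made and not a detail left open for a later analysis plan.

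**Working it through.** **Inputs from the protocol (Sample Size).** Two-sided alpha 0.05, power 0.90, standardised effect d = 0.71, attrition 10%, 48 per group.

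**Input not in the documents.** The within-group correlation r between T0 and T1 scores. It is assumed here at 0.3, 0.5 and 0.7.

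**Step 1: reproduce the plan's figure.** For a two-sample t-test with n per arm, the noncentrality is d × √(n/2) on 2n − 2 degrees of freedom. The smallest n with power of at least 0.90 is 43: 0.71 × √21.5 = 3.29, power 0.902. Allowing for attrition, 43 / (1 − 0.10) = 47.8, rounded up to 48. The stated sample size is reproduced exactly.

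**Step 2: add T0 as a covariate.** ANCOVA multiplies the residual variance by 1 − r². The noncentrality becomes 0.71 × √21.5 / √(1 − r²) on 2n − 3 = 83 degrees of freedom, and the interval narrows by the fraction 1 − √(1 − r²). With 43 per arm:

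| Analysis | Residual variance | Power at d = 0.71 | Power at d = 0.50 | Effect detectable with 90% power | CI narrower by |
|---|---|---|---|---|---|
| t-test | 1.00 | 0.902 | 0.63 | 0.707 SD | – |
| ANCOVA, r = 0.3 | 0.91 | 0.927 | 0.67 | 0.675 SD | 5% |
| ANCOVA, r = 0.5 | 0.75 | 0.964 | 0.75 | 0.613 SD | 13% |
| ANCOVA, r = 0.7 | 0.51 | 0.995 | 0.89 | 0.505 SD | 29% |

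The unadjusted 95% half-width is about 1.99 × √(2/43) = 1.99 × 0.216 = 0.43 SD. At r = 0.5 it becomes 0.43 × √0.75 = 0.37 SD. The column for d = 0.50 is an illustration of a smaller true effect, not a planning value of the protocol.

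**Step 3: size of a chance baseline gap.** Under simple randomisation the T0 difference has standard error √(2/43) = 0.216 SD. Then 0.2 / 0.216 = 0.93, so a gap above 0.2 SD in either direction has probability about 35%. Likewise 0.3 / 0.216 = 1.39, giving about 16% for a gap above 0.3 SD. Both apply per scale. A gap of 0.3 SD moves the expected unadjusted T1 difference by r × 0.3 = 0.09, 0.15 or 0.21 SD at r = 0.3, 0.5 or 0.7.

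**Step 4: grades, if they are balanced by design.** If a factor with correlation ρ to the outcome is perfectly balanced and then left out of the analysis, the size of the t-test tends to 2 × [1 − Φ(1.96 / √(1 − ρ²))]. This is about 4.0% at ρ = 0.3 and 2.4% at ρ = 0.5, against a nominal 5%. These are limiting values: they need perfect balance, an assumed ρ, and a role for grades that the protocol does not define.

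**The case against.** The strongest reply is that nothing here is an error. Under 1:1 randomisation the independent t-test is unbiased on average and holds its type I error. It is the test on which the sample size was based, and it delivers the planned power. All of that stands. A reader might infer that the primary test is invalid or the trial underpowered; step 1 shows otherwise for power, and randomisation secures validity.

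A reader might also take the 35% and 16% in step 3 as additional error. They are not: the t-test's standard error already allows for chance baseline differences over repeated trials. The figures describe the imbalance that one realised trial may show, which ANCOVA corrects and the t-test does not. They would also be smaller if randomisation balanced something that predicts T0, so steps 3 and 4 cannot both apply at full strength.

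It is tempting to say that omitting grades makes the test wrong. The protocol says only that questionnaire information helps the randomisation; it does not say that grades are a stratification or balancing factor. If they are, the consequence is a conservative test, not excess false positives.

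Nor can one say that T0 never enters a between-group test. Data Analysis gives no time point, so the independent t-tests may be run at T0 as well. A test at T0 would still not adjust the comparison at T1, which is the one that tests the intervention.

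Finally, the gain rests on an assumed correlation and is modest at r = 0.3. That is correct, and is why a range is shown.

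**Conclusion.** The point holds as a worthwhile improvement to a valid analysis. The protocol fixes an unadjusted comparison while holding the covariate most likely to sharpen it. At the planning effect of 0.71 SD with 43 evaluable per arm, power goes from 0.90 to between 0.93 and 0.995, and the interval narrows by about 5% to 29%, for correlations from 0.3 to 0.7. The benefit would matter more if the true effect were smaller than planned.

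This rests on the assumed correlation, on a roughly linear T0–T1 relation with a similar slope in both groups, and on T0 being unaffected by allocation. The last needs attention: Randomization and blinding places T0 after randomisation, at the same meeting at which students learn their group, and does not state explicitly which comes first.

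**What to change.** - In Data Analysis, make the primary analysis of each primary outcome an ANCOVA of the T1 total score on group, with that outcome's T0 score as covariate. Report the adjusted mean difference with its 95% confidence interval. Keep the independent t-test at T1 as a sensitivity analysis.
- State whether grades or other questionnaire variables are stratification or balancing factors. Add them as covariates only if they are.
- In Randomization and blinding, state that T0 is completed before students learn their allocation.
- Leave the sample size at 48 per group.

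The cost is small: no further students, assessments or software, since SPSS 26.0 fits ANCOVA, and one degree of freedom for each T0 covariate. The trial is already ethics-approved and registered, so the change may need a protocol amendment and a registry update. It should be made before outcome data are seen, because an adjustment added after an imbalance has appeared would look data-driven.

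### The paired before-after t-tests cannot isolate the effect of VCS, and the plan does not say that the between-group test decides, least of all for the dimension scores

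*Protocol*

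**What the plan says.** Data Analysis in the protocol sets out two families of tests on the three primary outcomes.

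- Between groups: "Independent t-tests will also be used to compare the levels of palliative care knowledge, ability, and attitudes between the intervention and control groups".
- Before and after: for overall scores and scores on the separate dimensions, compared before and after the VCS intervention, "researchers will use paired t-tests to assess the changes in these levels in the students".

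One threshold covers both: "A two-tailed p<0.05 is considered statistically significant". Neither family is called primary, supportive or descriptive. Dimension scores appear only in the sentence on paired tests, which does not say whether those tests are run in each arm or in all students together.

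The teaching sequence is given elsewhere in the protocol. Under Intervention Group: "Participants in the intervention group will receive the same 90 minutes of classroom teaching as the control group". Under Control Group, on that lesson: "This teaching session will mirror the key points and utilize the same case themes as those found in the VCS system". Under Intervention content: "After the 90-minute conventional classroom teaching, each participant will be assigned a unique code for accessing the VCS system". Data Collection places T0 before any teaching and T1 after the intervention, with nothing measured in between. The control group receives VCS after T1.

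**The concern.** Study design asks whether VCS improves these outcomes compared with conventional teaching, which is a question about the difference between the arms. The paired test asks whether scores moved between T0 and T1. In the VCS arm that movement has three sources: the lesson, answering the same instruments a second time, and VCS. No measurement falls between the lesson and VCS, so a paired test cannot separate them. The lesson covers the same content as VCS and can be expected to raise scores by itself.

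The wording nevertheless attaches the paired test to the VCS intervention and gives it the same significance threshold as the between-group test. If the between-group test were null and the paired test significant, the text would not stop a report from concluding that VCS worked. The gap is widest for the dimension scores, where the paired test is the only test named.

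**Working it through.** **1. The plan's own figure.** Sample Size gives a two-tailed independent t-test, alpha 0.05, power 0.90, effect size 0.71 and 10% attrition. With the noncentral t distribution, 42 per group gives power 0.895 and 43 gives 0.902, so 43 are needed. Then 43 / 0.90 = 47.8, rounded up to 48. The stated 48 per group reproduces. The trial is sized on the between-group test, and 43 is the expected number of completers per arm.

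**2. What each comparison estimates.** Let L be the mean gain from the lesson, R from retesting and V from VCS, taken as additive.

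- T0-T1 change, VCS arm: L + R + V
- T0-T1 change, control arm: L + R
- Difference between arms at T1 under randomisation: V

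The null hypothesis of the paired test in the VCS arm is L + R + V = 0. Only the between-arm contrast tests V = 0. Pooling both arms in one paired test does not help: with equal arms the mean change is L + R + V/2.

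**3. How often the paired test is significant when V = 0.** The protocol gives neither the shared gain g = L + R (in SD units) nor the T0-T1 correlation r, so both are assumed over a range. With equal SDs at T0 and T1, the standardised mean change is dz = g / √(2(1 − r)). The noncentrality is dz × √43, with 42 degrees of freedom and a two-sided critical value of 2.018.

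Worked case, g = 0.4 and r = 0.5: dz = 0.4 / √1 = 0.40; noncentrality 0.40 × 6.557 = 2.62; probability of p<0.05 = 0.727.

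| Shared gain g | r = 0.3 | r = 0.5 | r = 0.7 |
|---|---|---|---|
| 0 SD | 5% | 5% | 5% |
| 0.1 SD | 8% | 10% | 13% |
| 0.2 SD | 19% | 25% | 38% |
| 0.3 SD | 37% | 49% | 70% |
| 0.4 SD | 58% | 73% | 91% |
| 0.5 SD | 77% | 89% | 99% |

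**4. The between-group test under the same conditions.** In 40,000 simulated trials per setting (43 per arm, r = 0.5, V = 0, shared gains of 0, 0.2, 0.3, 0.5 and 0.8 SD), the independent t-test at T1 was significant in 4.7% to 5.1%. The shared gain cancels between the arms.

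**The case against.** The strongest reply is that the right test is already in the plan. The independent t-tests cover the same three outcomes, match the comparative aim and are the test used for the sample size. All of that stands. A reader might infer from the paired tests that the plan discards its control group or has no randomised comparison. The document does not support that, and an unadjusted between-group comparison at T1 is valid without any analysis of change.

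A second reply is that the protocol never says a significant paired test proves that VCS works, and that its mention of VCS may simply name the two time points. This reading is possible, and it is why the point concerns an unranked and unsuitable test rather than a stated false conclusion.

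Third, the percentages for g above zero are not type I errors of the paired test. Scores did change, and the test detects that correctly. The error arises only if the change is credited to VCS. This is right, and the table should be read that way.

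A reader might also infer that the authors will set one arm's paired p-value beside the other's and call the contrast an effect. The protocol states no such procedure, so an error rate for it is not charged to the plan.

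Finally, ranking of analyses is often left to an SAP, which is not shown here. That would answer a mere omission. Here the protocol itself states a test tied to VCS that cannot isolate VCS, and names no other for the dimension scores.

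**Conclusion.** The point holds in a limited form, as a should-fix. The plan contains a valid between-group test, but beside it sets paired tests at the same threshold, worded as a before-after assessment of VCS, and does not say which decides. For dimension scores only the paired test is named. Because T0 to T1 spans the shared lesson and a repeat assessment, a significant paired result says nothing specific about VCS.

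With no VCS effect and 43 completers, the VCS-arm paired test would be significant in 19% to 38% of trials at a shared gain of 0.2 SD and in 58% to 91% at 0.4 SD, against about 5% for the between-group test. The ranges reflect an assumed correlation of 0.3 to 0.7. The size rests on the assumed gain: at 0.1 SD the figure is only 8% to 13%. That the paired test cannot separate VCS from the lesson and retesting does not depend on these assumptions.

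**What to change.** In Data Analysis, state that all conclusions on VCS, for total and dimension scores, come from the between-group comparison of T1 scores adjusted for T0 (ANCOVA), in place of the unadjusted independent t-test. Report within-group change in each arm as mean and 95% CI, described as descriptive, and remove the paired t-tests as evidence of a VCS effect.

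The adjustment uses T0 scores already collected in both arms. It reduces residual variance by a factor of about 1 − r², which is 0.75 at an assumed r of 0.5. The downside is that within-group p-values can no longer be reported as effects. Design, sample size and data collection do not change. The edit should be made before outcome data are seen, so that the choice cannot appear to depend on the result.

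### Three unranked primary outcomes are each tested at 0.05 with no rule for success, and the stated power of 0.90 belongs to one unadjusted test

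*Protocol*

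**What the plan says.** The Primary Outcomes section of the protocol lists three instruments: the nurses' "Palliative Care Knowledge Scale", "The Undergraduate Nursing Students' Palliative Care Ability Assessment Questionnaire", and the Chinese FATCOD-B attitude scale. None is marked as the main one and no order of testing is given.

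Data Analysis gives the between-group test: "Independent t-tests will also be used to compare the levels of palliative care knowledge, ability, and attitudes between the intervention and control groups". It ends with a single threshold for all tests: "A two-tailed p<0.05 is considered statistically significant". A separate sentence adds paired before-after tests on overall and dimension scores.

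Sample Size describes one calculation, "employing a two-tailed independent t-test with an alpha level of 0.05, a power of 0.90, and an effect size of 0.71". With 10% attrition this leads to 48 students per group. It does not say which of the three outcomes the effect size refers to.

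No section states an adjustment for multiple primary outcomes, a testing order, or a rule for what counts as a positive trial. The aim in Study design joins the three outcomes with a plain conjunction, which describes the aim and is not a decision rule.

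**The concern.** Three parts of the plan do not fit together: three primary outcomes of equal standing, 0.05 for each, and a sample size for one test. What the trial's error rate and power are depends on a success rule that the protocol does not give.

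There are two obvious rules. If one significant outcome out of three is enough, the error rate is above 5%. If all three are needed, the error rate is safe but the power is below 0.90. Neither rule, used with the plan as written, gives both 5% error and 0.90 power.

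While the rule is open, it can be settled after the results are seen, and whichever scale reaches p<0.05 can be presented as a primary success. That bears directly on the trial's main conclusion.

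**Working it through.** **Inputs from the protocol.** Three primary outcomes (Primary Outcomes); two-sided 0.05 for each (Data Analysis); alpha 0.05, power 0.90, d = 0.71, 10% attrition, 48 per group (Sample Size); 1:1 allocation (Randomization and blinding).

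**Assumptions not in the protocol.** d = 0.71 holds on every outcome. The three outcomes share a common correlation, ranged from 0 to 0.8. There are 43 evaluable students per arm after attrition.

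**1. The plan's own figure.** For a two-sample t-test the noncentrality is d × √(n/2), with 2n − 2 degrees of freedom. At n = 42 per arm, power is 0.895. At n = 43, the noncentrality is 0.71 × √21.5 = 3.29 and power is 0.902. Then 43 / 0.90 = 47.8, so 48 per group. The stated size reproduces exactly, for one unadjusted test.

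**2. If any one outcome suffices, each at 0.05.** With independent outcomes and no true effect, the chance of at least one p<0.05 is 1 − 0.95³ = 0.143. Simulated t-tests with correlated outcomes give about 0.126 at correlation 0.5 and 0.098 at 0.8. The range is therefore about 10% to 14%.

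**3. If all three must pass, each at 0.05.** The chance that all three pass when at least one has no effect cannot exceed 5%, because that outcome alone passes at most 5% of the time. Joint power with 43 per arm is 0.902³ = 0.734 for independent outcomes. By simulation it is about 0.78 to 0.79 at correlation 0.5 and 0.83 at 0.8.

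**4. If any one suffices and error is controlled.** The Bonferroni threshold, which is also Holm's first step, is 0.05 / 3 = 0.0167.

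- Power for a given outcome at 0.0167 with 43 per arm is 0.800.
- The chance that at least one outcome passes is 1 − (1 − 0.800)³ = 0.992 if independent. By simulation it is 0.97 at correlation 0.3, 0.95 at 0.5, 0.92 at 0.7 and 0.90 at 0.8.
- Under the full Holm procedure, average power per outcome is about 0.88 at correlation 0 and 0.85 at 0.8. Holm rejects everything that Bonferroni rejects, so 0.80 is its floor.

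**5. Baseline adjustment.** With T0 as a covariate and T0–T1 correlation r, the effective effect size is 0.71 / √(1 − r²), tested with 83 degrees of freedom. The protocol gives no value for r.

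| Assumed r | Power at 0.0167, 43 per arm |
|---|---|
| 0.2 | 0.82 |
| 0.3 | 0.84 |
| 0.4 | 0.87 |
| 0.5 | 0.91 |
| 0.6 | 0.95 |

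**The case against.** The strongest defence has four parts.

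First, the protocol nowhere says that one significant outcome makes the trial positive. If each outcome is reported as its own claim, each claim keeps its 5%; if all three are required, joint error is at most 5%. This stands. A reader might infer that the trial's false-positive risk simply is 10% to 14%, but that figure belongs to the any-one rule, which the protocol neither adopts nor excludes.

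Second, the sample may be adequate. A reader might infer that 96 students are too few once error is controlled. For a claim on at least one outcome that is wrong: at 0.0167 the chance of at least one success stays at about 0.90 or higher for correlations up to 0.8. The shortfall is confined to a given outcome taken by itself and to the requirement that all three succeed.

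Third, the dimension scores might be thought to raise the error further. Data Analysis mentions them only in the sentence on paired before-after tests, not in the between-group comparison, so they contribute nothing to the 10% to 14%.

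Fourth, a multiplicity strategy is often left to the statistical analysis plan, which is not at hand. The absence of a named procedure would not by itself be a fault. But this protocol does fix a threshold for every test, fixes three primaries, and fixes the power on one test. A later adjustment would change the threshold stated in Data Analysis and leave the 0.90 in Sample Size untrue for a given adjusted test.

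**Conclusion.** The point holds in this form: the protocol fixes three unranked primary outcomes, 0.05 for each, and a single-test sample size, and gives no success rule. The sample-size arithmetic is correct, but its 0.90 describes one unadjusted outcome only.

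The consequence depends on the rule chosen: excess false-positive risk if any one outcome suffices without adjustment, or reduced joint power if all three are required. The power figures assume 43 evaluable students per arm and d = 0.71 on all three scales. The correlation range of 0 to 0.8 is also assumed, because the protocol gives no correlation. At higher correlations the excess error shrinks further.

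The missing success rule is the part that must be settled, and before any T1 data are seen. The power restatement follows from it.

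**What to change.** In Data Analysis, do one of the following:

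- apply Holm across the three between-group comparisons of total scores at T1, with overall two-sided alpha 0.05; or
- name one outcome as primary and make the other two secondary, in which case 0.90 at 0.05 stands for the named outcome at the planned effect size.

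In either case, label the before-after tests on dimension scores exploratory.

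In Sample Size, state that 0.90 applies to one unadjusted outcome. If Holm is chosen, add that power for a given outcome is at least 0.80 at d = 0.71 with 43 evaluable per arm.

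The cost is a few sentences and a less favourable stated power; no extra participants are needed. Adjusting the T1 comparison for the T0 scores, which Data Collection already provides, could recover power. How much depends on the T0–T1 correlation, so any such gain should be stated as a range (0.82 to 0.95 at 0.0167 for assumed correlations of 0.2 to 0.6) and not as a single figure.
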